## Abstract

**Background:**

Family-focused interventions promoting lifestyle behaviors such as physical activity and healthy eating can be effective strategies for obesity management in children. To maximize public health impact, there is an urgent need to develop innovative solutions to improve the scalability of childhood obesity management interventions. Stand-alone web-based interventions are easily administered but may be hindered by low participant engagement and limited support. A blended intervention that includes both facilitated web-based group sessions and self-guided resources may enhance engagement, thereby optimizing improvements in children’s health outcomes. However, the long-term effectiveness of stand-alone versus blended web-based interventions to manage childhood obesity has not yet been evaluated.

**Objective:**

The primary objective of this randomized controlled trial is to evaluate the long-term effectiveness of a blended, web-based, family-focused healthy living program (Family Healthy Living Program [FHLP]) compared to an active control (self-guided web-based educational resources) in lowering BMI *z* scores in children with overweight or obesity over 12 months. The secondary objective is to examine intervention effects on children’s physical activity, dietary behaviors, and health-related quality of life as well as parental self-efficacy and motivation to support children’s lifestyle behaviors.

**Methods:**

This single-blind 2×4 trial aims to recruit 278 parent-child dyads across Canada to be randomly assigned to the FHLP intervention group or an active control group (1:1 ratio). The 10 weeks of FHLP activities have been designed based on the multiprocess action control framework to support children and parents in learning behavioral change skills that will enable them to improve their healthy lifestyle behaviors, and the FHLP delivery has been piloted previously. Families in the intervention group will receive weekly web-based synchronous group sessions and access to additional resources and suggested activities. Families in the control group will receive access to 10 weeks of self-guided web-based educational resources only. Outcomes, including child’s height and weight, daily physical activity, dietary behaviors, health-related quality of life, and parental support, will be measured via questionnaire at 4 assessment time points over 1 year (ie, baseline, 10 wk, 6 mo, and 12 mo). Intervention engagement and attrition will also be recorded. Multiple linear regression models will be used to examine the effectiveness of the FHLP intervention compared to stand-alone web resources only.

**Results:**

This study was funded in 2020, with 270 participants enrolled between January 2021 and May 2024. The 12-month data collection period ended in June 2025 and data analysis is currently underway. Study results are expected to be published in winter 2025. Results will be disseminated via conference presentations, peer-reviewed publications, and other media channels.

**Conclusions:**

The blended web-based FHLP intervention has the potential to become a scalable solution for the prevention of obesity and related health conditions.

**Trial Registration:**

ClinicalTrials.gov NCT06777888; https://www.clinicaltrials.gov/study/NCT06777888

**International Registered Report Identifier (IRRID):**

DERR1-10.2196/76837

## Introduction

### Background and Rationale

Childhood obesity is a prevalent pediatric health issue linked to a range of physical and psychological problems, including type 2 diabetes, hypertension, sleep apnea, and low self-esteem, all of which contribute to a diminished quality of life during childhood [1-3]. In Canada, more than 30% of children are classified as overweight, defined based on BMI ≥85th percentile for their age and sex [1]. Without effective interventions, these children have a high risk of remaining overweight into adolescence and adulthood [4]. As a result, fostering healthy eating habits and encouraging physical activity during childhood has become a central focus for policymakers and public health initiatives at the global, national, and provincial levels [5-7].

Family-focused behavioral obesity management interventions that include both parents and children as corecipients have been shown to be an effective approach for promoting healthy lifestyles and achieving weight control in children [8,9], particularly when the intervention content is grounded in behavioral theory [10]. Several randomized controlled trials have demonstrated that family-focused behavioral interventions delivered in person can be effective strategies in improving children’s lifestyle behaviors and reducing BMI *z* scores [11-13]. However, to enhance their public health impact, such interventions must be delivered through scalable and accessible methods.

Leveraging the internet to deliver these interventions can be an innovative strategy to enhance program accessibility and scalability, making it easier for families to participate regardless of their geographic location [14]. Previous studies have shown that internet-based programs can be effective in improving lifestyle behaviors and clinical outcomes, including BMI [15,16]. However, a limitation often observed in self-guided, asynchronous web-based interventions (with no human support) is reduced engagement over time [17]. By contrast, synchronous web-based sessions (delivered using video chat) may provide distinct advantages, such as fostering engagement through real-time interaction, personalized support, and opportunities for families to connect and share experiences. These sessions retain the scalability and flexibility of internet-based interventions while offering live interaction, which may enhance motivation, promote accountability, and improve adherence to the program [18]. This could make synchronous delivery a powerful and adaptable option for managing childhood obesity effectively.

Drawing on the evidence supporting the effectiveness of family-based interventions and use of the internet for program delivery, the research team partnered with stakeholders (the Childhood Healthy Living Foundation and the British Columbia Ministry of Health) to develop a 10-week early intervention lifestyle management program (Family Healthy Living Program [FHLP]) that combines web-based resources with weekly live, interactive group sessions led by trained facilitators. This intervention targets families with children aged 8 to 12 years who are above the healthy weight trajectory (BMI ≥85th percentile for age and sex). Interventions aimed at this age group are particularly impactful, as prepubertal children have a greater potential to return to a healthy growth pattern [19,20]. Extensive stakeholder consultation was conducted with more than 100 health care professionals to develop an evidence-based 10-week family-focused intervention involving both parent- and child-specific interactive activities. The FHLP intervention was designed to align with existing best practices in the clinical and public health setting, complement an existing childhood obesity management clinical intervention in British Columbia, and meet the needs of diverse families and communities [21]. The FHLP aims to support children who are off the healthy weight trajectory by managing overweight and preventing progression to obesity through targeting 5 behavioral domains: physical activity, healthy eating, sleep, media use, and mental well-being.

The FHLP was designed using the multiprocess action control (M-PAC) framework, a meta-theoretical behavior change framework emphasizing a social cognition approach to intention formation (reflective processes), the adoption of action control through self-regulation (regulatory processes), and the action control maintenance phase once a behavior becomes habitual and self-identified (reflexive processes) [22,23]. One advantage of the M-PAC framework is its ability to address the intention-behavior gap, which poses a particular challenge for childhood obesity interventions because almost all families enter these programs already intending to adopt a healthy lifestyle but often struggle to translate this intention into sustained behavior change [22,24,25]. Addressing this intention-behavior gap can therefore improve the effectiveness of physical activity interventions [23,26]. Thus, the FHLP curriculum begins with intention formation (physical and mental health benefits of physical activity as well as perceived capability), then moves into action control adoption (restructuring the physical and social environment to create opportunities for physical activity, goals and planning, and feedback and monitoring), and concludes with action control maintenance (habit formation and identity formation).

The FHLP intervention was initially piloted in 2018 [21] and delivered in person at community sites across British Columbia. The content has since been adapted for delivery as a blended web-based intervention, and previous evaluation showed a positive impact on children’s lifestyle behaviors and parental support in the short term [27,28]. However, the FHLP intervention has yet to be evaluated in a randomized controlled trial, and the long-term effectiveness of the intervention and its impact on children’s anthropometry have not been examined.

### Objectives

The primary objective of this study is to evaluate the effectiveness of the synchronous web-based FHLP intervention compared to an active control group in lowering BMI *z* scores in children (aged 8-12 y) with BMI ≥85th percentile for age and sex over a 12-month period. The secondary objectives include evaluation of the effectiveness of FHLP compared to the active control in improving lifestyle behaviors and health-related quality of life in children (aged 8-12 y) with BMI ≥85th percentile for age and sex, as well as parental self-efficacy and motivation to support their child’s healthy living behaviors. The trial hypotheses are that the FHLP intervention will result in significantly greater reduction in BMI *z* scores than the active control and that intervention participants will show greater improvements across all domains than those in the control group.

## Methods

### Trial Design

This study is a single-blind randomized controlled trial (ClinicalTrials.gov NCT06777888) with a 2×4 design (Figure 1). Participating households will be randomly assigned in a 1:1 ratio to 2 groups: FHLP intervention and control. Data will be collected at 4 assessment time points: baseline (wk 0), after the intervention (wk 10), 6-month follow-up (wk 26), and 12-month follow-up (wk 52; Figure 1). The intervention will be delivered via video chat in 3 regions across Canada (British Columbia, the prairie provinces, and Ontario), with the central site located at the University of Victoria in British Columbia.

**Figure 1 figure1:**
[figure not shown]
Overview of the study design and assessment timeline. FHLP: Family Healthy Living Program.

Trial preparation, implementation, and evaluation will adhere to the CONSORT (Consolidated Standards of Reporting Trials) criteria [29], and the trial protocol will adhere to the SPIRIT (Standard Protocol Items: Recommendations for Interventional Trials) guidelines [30]. Data collection began in January 2021 and was completed in June 2025.

### Eligibility Criteria

Child participants must be aged 8 to 12 years, have BMI ≥85th percentile for age and sex, and have at least 1 primary caregiver (parent or guardian) who agrees to participate in the study along with the child. Exclusion criteria will include the inability to communicate (speak, read, and write) in English and any conditions that prevent children from being physically active.

### Recruitment

Participants will be recruited from 3 regions across Canada (British Columbia, the prairie provinces, and Ontario) using advertising via social media; local community newsletters; posters and rack cards within communities; and direct mailings to physician offices, health clinics, and allied health professionals. Interested parent-child dyads will be screened for eligibility by a trained research assistant at the central site (University of Victoria in British Columbia).

During the consent process, participants will be made aware of the differences between the 2 groups and informed that they will be randomly assigned to either the full intervention or the web resources only. Participants from both groups will be offered technical support from the research coordinator if needed for viewing web-based content, using the Fitbit Inspire tracker, or accessing the web-based questionnaires.

### Assignment of Interventions and Blinding

Participating households will be randomly assigned to the FHLP intervention or the active control group. To reduce selection bias, the centralized randomization process will be managed by a research coordinator not directly involved with intervention delivery. The research coordinator will use computer-generated random numbers to assign the participants to either the intervention or control group. Participants will not be stratified because the population is assumed to be inherently homogeneous with respect to location due to the web-based nature of the program delivery. After randomization, data will be collected electronically via REDCap (Research Electronic Data Capture; Vanderbilt University) automated invitations to reduce response bias. Other research team members, including the principal investigator, coinvestigators, and data analysts, will be blinded to group assignment to minimize detection bias and ensure impartiality in decisions regarding trial activities.

### Participant Timeline and Data Collection

The intervention period will be 10 weeks; the full assessment duration will be 12 months. Web-based questionnaire assessments will be completed at baseline and at 10-week, 6-month, and 12-month intervals after randomization (Figure 1). The assessments will include self-reported height and weight measurements and 7 days of step counts for each child as measured by Fitbit Inspire activity trackers. Questionnaire data will be collected and managed using SurveyMonkey and REDCap tools hosted at the University of Victoria. REDCap is a secure, web-based software platform designed to support data capture for research studies [31,32]. Survey responses will be stored on a secure network drive at the University of Victoria. Participants may choose to discontinue their participation at any point; data completion will be encouraged by multiple personalized email reminders and compensation at each assessment time point.

### Sample Size

The parameters used for sample size calculation are based on the results of a published randomized controlled trial evaluating the effectiveness of a family-based intervention in reducing BMI *z* scores compared to control [33]. The required sample size was estimated at 232 children, using a 2-arm, parallel-group design with 80% power. On the basis of previous research [17,33], the attrition (loss at follow-up) is expected to be similar between the groups (20%). In sum, the trial aimed to recruit a study population of 278 participants, which accounts for an attrition rate of 20%. In practice, 270 participants were successfully enrolled.

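### The Sample Size section says a target of 278 allows for 20% attrition; it allows for about 16.5%, and keeping 232 children after 20% loss needs 290

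*Protocol article*

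**What the plan says.** The Sample Size section of the protocol article gives four numbers in sequence.

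- The requirement: "The required sample size was estimated at 232 children, using a 2-arm, parallel-group design with 80% power".
- The expected loss: "the attrition (loss at follow-up) is expected to be similar between the groups (20" percent).
- The target: "In sum, the trial aimed to recruit a study population of 278 participants, which accounts for an attrition rate of 20" percent.
- The outcome of recruitment: "In practice, 270 participants were successfully enrolled".

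Allocation is equal (Trial Design: "Participating households will be randomly assigned in a 1:1 ratio to 2 groups: FHLP intervention and control"), so 232 means 116 per arm. The effect size, standard deviation, significance level and sidedness are not printed; the section refers to another trial for them ("The parameters used for sample size calculation are based on the results of a published randomized controlled trial"). The Methods paragraph of the abstract repeats the target, without any statement about attrition or power: "This single-blind 2×4 trial aims to recruit 278 parent-child dyads across Canada".

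**The concern.** An attrition rate is a proportion of the children enrolled. To have a required number left at the end, that number is divided by one minus the rate. The printed target looks instead as if the rate had been added on top of the requirement, which always gives too few. If so, the section claims cover for 20% loss that its target does not provide, and enrolment eight below that target (278 − 270) widens the gap.

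What is at stake is the accuracy of a design statement. A reader who takes the section at its word would believe that the planned sample still reaches the stated requirement after the planned loss. It does not, and the error runs in the favourable direction.

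**Working it through.** **Inputs, all from the Sample Size section:** required number 232; attrition 20%; target 278; enrolled 270; power 80%. The 232 is taken as given. It cannot be re-derived because its parameters are not printed, and the attrition check does not need them.

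**1. Reproducing the printed target.**
- Required × (1 + attrition) = 232 × 1.20 = 278.4, which rounds to 278.
- The article gives no other basis for 278 and no other attrition rate.

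**2. The target that keeps 232 after 20% loss.**
- Required / (1 − attrition) = 232 / 0.80 = 290, or 116 / 0.80 = 145 per arm.
- Check: 290 × 0.80 = 232 exactly.
- Shortfall of the target: 290 − 278 = 12. Shortfall of the enrolment: 290 − 270 = 20.

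**3. What remains after 20% loss, and how much loss each number can absorb.** The largest tolerable loss is 1 − 232 / N.

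| Recruited N | Left after 20% loss | Largest loss that keeps 232 |
|---|---|---|
| 290 | 232 | 20.0% |
| 278 (target) | 222.4 | 16.5% |
| 270 (enrolled) | 216 | 14.1% |

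**4. Illustration of the effect on power.** This step needs assumptions that the article does not state: two-sided alpha 0.05, an unadjusted comparison of two means among completers, and exactly 80% power at 116 per arm. It uses the normal approximation.

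- Implied standardised difference: (1.960 + 0.842) × √(2/116) = 0.368.
- Power with n per arm: Φ(0.368 × √(n/2) − 1.960).
- n = 111.2 (222.4 in total): 78.3%.
- n = 108 (216 in total): 77.1%.

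Under one-sided alpha 0.05 the implied difference is 0.326, and the two power figures are 78.5% and 77.5%. The loss is 2 to 3 percentage points either way.

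**The case against.** Three points can be made for the plan.

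**The planned analysis does not use completers only.** The Data Analysis section specifies a mixed model on all available data, adjusted for baseline BMI *z* score, with multiple imputation if data are missing at random. Children lost before 12 months may still contribute values at week 10 or 6 months. If 232 was derived for an unadjusted comparison, a baseline–outcome correlation of only about 0.26 would offset the fall from 232 to 216, since 1 − r² = 216/232 gives r = 0.26. If 232 already allowed for adjustment, that offset is gone. The article does not say which. This part stands as a limit on any power figure. It does not rescue the sentence in question, because the Sample Size section does not rely on the model. It sets 232 as the requirement, makes its own explicit allowance for loss, and computes that allowance wrongly.

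**The 20% might mean 20% added to the requirement.** The section's wording rules this out, since it speaks of an attrition rate and of loss at follow-up.

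**Recruitment and data collection are over, and the 270 is openly reported.** Both are true. Nothing in randomisation, outcomes or analysis depends on 278, and a condensed article need not recompute power after falling slightly short of its target. This bears on how serious the error is, not on whether the sentence is right.

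A reader might go further and infer that the trial has only 77% power, that a null result is bound to be over-read, or that the abstract's 278 is also an error. The documents support none of these. The 77% depends on an alpha, a sidedness and a test that are not stated. How a null result is read will depend mainly on its confidence interval, and 2 to 3 points of power would hardly change that. The abstract reports the recruitment target that was set and claims nothing about attrition.

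**Conclusion.** The statement is wrong as written, and the error is minor. A target of 278 does not account for 20% attrition from a requirement of 232; it allows for about 16.5%, and the 270 enrolled allow for about 14.1%. For 20%, 290 would have been needed. This conclusion uses only figures printed in the Sample Size section and rests on no assumption beyond reading attrition as a proportion of those enrolled.

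The consequence for power is small and can only be illustrated. It is not evidence that the trial is materially underpowered.

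**What to change.** Correct the Sample Size section only. Suggested content:

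> Keeping 232 children after 20% attrition would have required 232 / 0.80 = 290. The recruitment target of 278 allowed for attrition of about 16.5%. With 270 enrolled, 232 are retained only if attrition is no more than about 14%.

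If a power figure is added, label it as illustrative and state its assumptions beside it: two-sided alpha 0.05, an unadjusted two-group comparison of completers, and exactly 80% power at 232, giving about 78% at 222 and 77% at 216 (about 78.5% and 77.5% at one-sided 0.05). Since 12-month data collection has ended, the retention achieved and the confidence interval for the primary comparison will tell readers more than a projection.

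Leave 278 in the abstract as the target actually set. No extra enrolment is proposed, and conduct and analysis do not change. The cost is a few sentences of text and a slightly less favourable description of the design.

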### Intervention

The FHLP intervention aims to target children who are off the healthy weight trajectory, with the goal of managing overweight and preventing progression to obesity. FHLP curriculum activities have been designed to support children and parents in learning behavioral change skills that will enable them to improve their health-related lifestyle behaviors. The details of the intervention content have been previously published [21]. Families attend weekly 2-hour web-based healthy living group sessions comprising family-based and parent-only components. Family-based components consist of interactive lessons and active games to keep children engaged in learning and enhance the reflexive processes that lead to habit formation. For the final 30 minutes of each session, parent-only components focus on food- and physical activity–related practices and strategies for improving the home environment.

The FHLP intervention will be delivered by a team of 2 facilitators with backgrounds in nutrition or physical education. These individuals will receive training from the centralized research team (based at the University of Victoria), including attending FHLP sessions delivered in British Columbia via video chat by the Childhood Healthy Living Foundation. The facilitators will be participants’ main point of contact during the 10-week intervention and will call each enrolled family (via telephone or video chat) individually before the first group session to orient them to the program. They will send weekly email reminders for group sessions and reach out to participants following absences.

During the 10-week intervention, the facilitators will deliver 1 individual orientation call and 9 weekly group sessions over Zoom (Zoom Video Communications, Inc). Weekly group sessions will follow the FHLP curriculum with modules on healthy eating, physical activity, behavior change skills, mental health, parenting practices, sleep routines, and media use. Participants will be provided with a physical kit containing hard-copy binders of the session handouts along with materials to use during session activities (eg, jump ropes, water bottles, juggling scarves, and hacky sacks). Throughout all sessions, the facilitators will accentuate behavioral change skills (cognitive and behavioral regulation processes) such as goal setting and monitoring. One group session will include a “healthy eating Q&A” led by a registered dietitian in addition to the facilitators; participants will also have the option to attend up to 3 web-based live cooking classes led by a registered dietitian and child assistant.

In addition to the facilitated weekly sessions and cooking classes, participants in the intervention group will have access to a self-guided web-based family portal offering additional resources and information, healthy recipes, articles for parents, videos, and suggested healthy eating and physical activities. The portal will also serve as a repository of materials covered in each session, maximizing flexibility in terms of participants interacting with intervention content.

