### Active Control Group

It is an ethical imperative for long-term trials of health promotion interventions to ensure that the control group also receives essential information, which in this case would be education about childhood obesity management. To match the weekly intervention delivery frequency, the active control group will be given access to a similar secure portal where they can view weekly educational content aligned with the FHLP topics. This information is based on the FHLP curriculum and relevant information and resources from Canadian public health agencies (eg, Canada’s Guide to Healthy Living, Canada’s Food Guide, and Canada’s Physical Activity Guide). These materials are guideline based, user-friendly, and visually appealing; in addition, they include child-specific content.

At baseline, a member of the research team will meet with each control participant for a 10- to 15-minute video meeting to orient parents to the portal and ensure that they have sufficient internet literacy to access the resources. However, the control group will not receive other personal contact, such as the FHLP facilitated group sessions, physical kits, web-based cooking classes and Q&A sessions, regular check-ins, or email reminders to access the resources. All families in both study groups will maintain the same delivery schedule (10 weeks in total; Figure 1).

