### Data Analysis

#### Overview

All analyses will be intention to treat and will include all participants with available data. Patterns of missing data in the study groups will be examined, and multiple imputations will be applied to address missing data if data are missing at random. Generalized linear mixed models will be used to compare the effectiveness of the 2 treatments in improving the primary outcome, BMI *z* score, over time. The models will include fixed effects for treatment group, time, and group×time interaction; in addition, they will adjust for baseline BMI *z* score and child’s sex. A random intercept will be included to account for within-participant correlations across repeated measures. Similar to the primary outcome analysis, generalized linear mixed models will be used to examine changes in secondary outcomes over time. Models will adjust for the baseline value of the outcome, child’s sex, and parent’s relationship to the child; in addition, a random intercept will be included to account for repeated measures.

Previous research has shown that parental involvement in child interventions can differ in ways that affect behavioral and weight-related outcomes [55]. Including this variable makes it possible to control for these potential sources of variability in the generalized linear mixed models.

In line with the sex- and gender-based analysis framework of the Canadian Institutes of Health Research [56], which encourages the thoughtful integration of sex and gender into health research, we have taken steps to reflect sex and gender considerations in our analysis plan. Specifically, we will adjust for child sex assigned at birth where biological differences may be relevant to health outcomes (eg, BMI trajectories). In the exploratory analysis, descriptive analyses will be conducted to explore whether intervention effectiveness differed between children’s gender or sex in the treatment group.

Engagement metrics will primarily be examined in subgroup and dose-response analyses. However, engagement may play a role in treatment effectiveness. Therefore, its potential inclusion as a covariate in secondary models will be explored. These exploratory analyses will help clarify the mechanisms underlying intervention impact.

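### FHLP is delivered in facilitated groups and control individually, but the stated models and sample size make no allowance for correlation within FHLP session groups

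*Protocol article*

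**What the plan says.** The unit of randomisation is the household: "Participating households will be randomly assigned in a 1:1 ratio to 2 groups: FHLP intervention and control". Delivery then differs by arm.

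- **FHLP arm** (protocol article, Intervention): "the facilitators will deliver 1 individual orientation call and 9 weekly group sessions over Zoom". Sessions last 2 hours, combine family and parent-only parts, and are run by a team of 2 facilitators, who are the families' main contact.
- **Control arm** (Active Control Group): after one short individual orientation meeting, families use a self-guided portal, and "the control group will not receive other personal contact, such as the FHLP facilitated group sessions".
- **Rationale** (Background and Rationale): synchronous sessions in general may bring benefits that include "personalized support, and opportunities for families to connect and share experiences".
- **Analysis model** (Data Analysis, Overview): generalized linear mixed models with group, time, their interaction and covariates. The one random effect named for the primary outcome is this: "A random intercept will be included to account for within-participant correlations across repeated measures". The secondary models likewise have one random intercept for repeated measures.
- **Sample size** (Sample Size): "The required sample size was estimated at 232 children, using a 2-arm, parallel-group design with 80% power". The only stated adjustment is for attrition.

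The article gives no session-group or facilitator effect, cluster-robust variance, ICC, group size or design effect.

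**The concern.** Randomising households individually protects the comparison from allocation bias. It does not make outcomes independent once families in one arm are treated together. Children who share sessions may come to resemble each other through group dynamics, facilitator handling or timing. A participant intercept absorbs correlation between visits of the same child, not correlation between different children.

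If that between-child correlation is positive, the FHLP arm carries less information than its head count suggests. The planned model would then give a standard error for the group difference that is too small, with p-values and intervals that are too favourable. The same model form is used for the secondary outcomes. The stated 80% power would be optimistic for the same reason.

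**Working it through.** **Inputs from the protocol article.** 232 children required at 80% power; 278 targeted; 270 enrolled; 20% attrition; 1:1 allocation. Completers at that attrition: 270 × 0.8 = 216, or 108 per arm.

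**Inputs assumed.** Two-sided alpha of 0.05 (not stated); m = 6 to 15 families per session group, of whom 80% are retained; ICC = 0.01 to 0.10 for the baseline-adjusted outcome; equal group sizes; equal total variance in the arms; normal approximation.

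**Step 1: the plan's own figures.** The 232 cannot be reproduced forwards, because effect size and SD come from a cited trial ("The parameters used for sample size calculation are based on the results of a published randomized controlled trial"). Back-solving with 116 per arm gives

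d = (1.960 + 0.842) × √(2/116) = 0.368.

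The target of 278 is 232 × 1.2 = 278.4, so attrition alone accounts for it and no further inflation is visible. (Whether 1.2 is the right attrition factor is a separate matter.)

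**Step 2: power under independence.** With 216 analysed: Φ(0.368 × √(216/4) − 1.960) = Φ(2.703 − 1.960) = 77.1%.

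**Step 3: clustering in one arm.**

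- FHLP design effect: DE = 1 + (0.8m − 1) × ICC
- Variance of the difference relative to independence: R = (1 + DE)/2
- True SE / modelled SE = √R
- Actual type I error of the planned test: 2 × [1 − Φ(1.960/√R)]
- Power of a correctly sized test: Φ(2.703/√R − 1.960)

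For m = 10 and ICC 0.05: DE = 1 + 7 × 0.05 = 1.35; R = 1.175; √R = 1.084. Type I error is 2 × [1 − Φ(1.808)] = 7.1%. Power is Φ(2.494 − 1.960) = 70.3%. Back-solving d from the t distribution instead gives 0.369 and power of about 71%.

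| m | ICC | DE | SE ratio | Type I | Power, 216 analysed |
|---|---|---|---|---|---|
| 6 | 0.01 | 1.04 | 1.01 | 5.2% | 76.4% |
| 10 | 0.01 | 1.07 | 1.02 | 5.4% | 75.7% |
| 10 | 0.02 | 1.14 | 1.03 | 5.8% | 74.3% |
| 10 | 0.05 | 1.35 | 1.08 | 7.1% | 70.3% |
| 10 | 0.10 | 1.70 | 1.16 | 9.2% | 64.3% |
| 15 | 0.10 | 2.10 | 1.24 | 11.5% | 58.4% |

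**Step 4: sensitivity to retention.** If all 10 families per group are counted, with no retention factor, ICC 0.05 gives DE 1.45, type I error 7.7% and power 68.5% at 216 analysed. The exact figures move with such choices; the direction does not, provided the ICC is positive.

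**The case against.** The strongest reply is that the harm depends on quantities the article does not give. Without a positive ICC nothing is understated, and at ICC 0.01 the effect is trivial: with 10 families per group, a test at 5.4% rather than 5%. Several features point towards a low ICC for the primary outcome. Each parent measures the child at home, the model adjusts for baseline BMI *z* score, the curriculum is common, facilitators are trained centrally, and week 52 falls 42 weeks after the 10-week programme ends. Enrolment is closed, so the sample size cannot change. The article is condensed, and a separate analysis plan could add a group term.

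Most of this stands as a limit on size. It does not remove the point. None of those features shows the ICC to be zero, and secondary outcomes may have different ICCs. The article does not leave the random-effects structure open: it specifies one for the primary model and one for the secondary models, and neither fits the delivery it describes. The analysis can still be changed, since the article reports it as under way.

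A reader might be tempted to infer more than the documents support:

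- **That the FHLP variance is in fact understated.** This holds only if within-group correlation is positive.
- **That each family stayed in one fixed group with its own facilitators.** Weekly sessions and follow-up of absences suggest stable groups, but the article does not say so. If one pair ran every group, facilitators would not distinguish the groups.
- **That interaction between families is the stated mechanism of FHLP.** The remark on families connecting is a hedged, general one about synchronous delivery. The programme's own mechanism is given as the multiprocess action control framework.
- **That group membership is already on file.** The engagement section records how many sessions a family attended, not which group it joined.

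**Conclusion.** The point holds in conditional form. The design is partially nested, and neither the stated models nor the stated power calculation allows for it. If outcomes are positively correlated within session groups, the SE of the group difference is understated and power overstated, from negligibly (about 1% of the SE) to materially (about 24%) over the assumed range. The corresponding type I error is about 5.2% to 11.5%.

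All these figures are illustrative. They rest on assumed group sizes, ICC and alpha, and the power figures also on a back-solved effect size. An allowance within the cited trial's parameters cannot be ruled out, but none is stated. This is a should-fix: the remedy is standard and cheap. If the ICC is near zero the result will barely change, whereas omitting the term when the ICC is material would make the evidence for FHLP look stronger than it is.

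**What to change.** Before any unblinded analysis:

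1. Add to the primary and secondary models a random effect for FHLP session group in the intervention arm only, with controls as singletons, arm-specific residual variance, and Satterthwaite or Kenward-Roger degrees of freedom. With about 135 FHLP families in groups of 10 there would be only some 13 or 14 groups, so the small-sample correction matters.
2. Keep the term whatever its significance, and report the estimated ICC.
3. State in the Sample Size section that the 80% power assumed independent children.
4. Confirm that each family's assigned group can be recovered from delivery records.
5. Protect the analyst blinding described under Assignment of Interventions and Blinding, since a group identifier present in one arm only reveals that arm. For example, give controls dummy singleton codes and finalise the model code before the real identifiers are merged.

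Cost: slightly wider intervals, fewer degrees of freedom, and the extra handling of group identifiers. No new outcome data are needed, but group membership must be recoverable.
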